### Statistical analysis

Statistical analyses will be performed using STATA and SPSS. Methylation and RNA expression analyses will be conducted using R (EdgeR, DESeq2, Minfi).

Descriptive statistics will be used to analyze the number of ongoing pregnancies, miscarriages, and live births following autotransplantation of cryopreserved and thawed ovarian tissue, as well as the number of primordial follicles, time to pregnancy, and time to live birth. Continuous variables will be summarized as means with standard deviations (SD) or medians with interquartile ranges (IQR), depending on data distribution. Categorical variables will be summarized as percentages.

Associations will be assessed using Spearman’s correlation coefficient, including relationships between age at cryopreservation, hormone levels, and the number of primordial follicles.

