### Study period

Recruitment began in January 2024, and the study is expected to continue until 2050.

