### Sample size calculation

Given the exploratory nature of this study, the live birth rate following OTC in women with TS is unknown. Power calculations are therefore based on data from female cancer survivors treated with gonadotoxic therapy. In this group, pregnancy rates following transplantation of thawed ovarian cortical tissue are approximately 50% and live birth rates around 35% [26, 31–33]. Spontaneous miscarriage occurs in an estimated 30–45% of TS pregnancies with autologous oocytes [11, 34]. Based on these figures, approximately seven patients would require OTC for one live birth to occur. Using the formula from Hulley et al. [35] for dichotomous outcomes (expected LBR of 0.25; a confidence interval width of 0.2; and a significance level (α) of 0.025) the required sample size is 72, corresponding to 18 expected live births. We aim to include 100 girls undergoing OTC. Data from participants lost to follow-up will be included where possible.

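### Time to pregnancy and time to live birth are assigned plain means or medians with no method for censored times, which biases them short under staggered follow-up

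*Protocol article*

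**What the plan says.** The Statistical analysis section of the protocol article assigns descriptive statistics to ongoing pregnancies, miscarriages and live births after autotransplantation, "as well as the number of primordial follicles, time to pregnancy, and time to live birth". The next sentence gives the summary measures: "Continuous variables will be summarized as means with standard deviations (SD) or medians with interquartile ranges (IQR), depending on data distribution". Categorical variables become percentages. The only other method named for clinical data is correlation: "Associations will be assessed using Spearman’s correlation coefficient". Censoring, survival curves and cumulative incidence are not mentioned.

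Four other statements bear on how long women will be observed:

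- Study period: "Recruitment began in January 2024, and the study is expected to continue until 2050". The abstract adds that recruitment is ongoing.
- Study population: girls enter at age 2–17.
- Ovarian tissue autotransplantation: tissue is returned only when pregnancy is being planned and transplantation is indicated.
- Sample size calculation: "Data from participants lost to follow-up will be included where possible". No censoring rule accompanies this.

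**The concern.** The two times are handled in the same way as a follicle count, which every woman with analysed tissue has. A time to live birth is different. A woman who has not yet had a live birth when follow-up ends has no value, only a lower limit. A mean or median can deal with her in two ways:

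- Leave her out. The summary then covers only observed successes, and slow successes are the ones most likely to be cut off.
- Enter her follow-up time as if it were an event time. That value is never longer than her true time and is usually shorter.

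Neither gives an unbiased time. Women transplanted close to the end of the study or lost early are the most affected. The article says its findings should support counselling of girls and families, and a median based on observed successes would tell them that success comes sooner than it does. A crude percentage with the same unequal follow-up would understate eventual success if women with little follow-up stay in the denominator.

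**Working it through.** **1. The plan's own figures.** Inputs from the Sample size calculation section are a live birth rate p = 0.25 and an interval width W = 0.2, with α = 0.025 read as per tail, so z = 1.96.

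N = 4z²p(1−p)/W² = 4 × 3.8416 × 0.1875 / 0.04 = 72.03, which agrees with the stated 72.

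Expected live births are 72 × 0.25 = 18, as stated. The calculation uses a proportion only, and no event time enters it.

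**2. Is follow-up staggered?** From 2024 to 2050 is 26 years. A girl aged 2 at entry in 2024 is 28 at the end of the study, and one aged 17 is 43. Girls who enter later at the same age are younger in 2050. Transplantation waits for pregnancy planning in adulthood, so time from transplantation to study end will differ widely between women. Loss to follow-up adds to this.

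**3. Size under assumed values.** The documents give no distribution of times, no loss rate and no length of follow-up after transplantation, so everything here is assumed. Let 35% eventually succeed, with exponential times of mean 2 years, and let follow-up C be uniform from a to b years.

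- True median among eventual successes: 2 × ln 2 = 1.39 years.
- Share of eventual successes seen: P(T ≤ C) = 1 − 2(e^(−a/2) − e^(−b/2))/(b − a).
- Event-only median: the point at which half of the observed-event density, 0.5·e^(−t/2)·P(C ≥ t), has accumulated (solved numerically).

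Follow-up 0.25–4 years:
- Share seen: 1 − 2(0.8825 − 0.1353)/3.75 = 0.60.
- Crude proportion: 0.35 × 0.60 = 21%, against 35%.
- Event-only median: 0.75 years, 46% below 1.39.

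Follow-up 0.5–12 years:
- Share seen: 1 − 2(0.7788 − 0.0025)/11.5 = 0.865.
- Crude proportion: 0.35 × 0.865 = 30%, against 35%.
- Event-only median: 1.15 years, 17% below 1.39.

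The crude proportions assume that every transplanted woman is in the denominator however short her follow-up.

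**4. Other assumed values.** With 25% or 50% ever succeeding, a mean time of 1.5 to 3 years and follow-up uniform over 0–5 or 0–10 years, the event-only mean is 0.96 to 1.93 years against true means of 1.5 to 3.0. The shortfall runs from 17% (1.24 against 1.50) to 58% (1.26 against 3.00), and the mean is short in every case.

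**5. What the event-only median tracks.** Take a constant hazard, fixed follow-up F and cumulative incidence c by F. Then λ = −ln(1 − c)/F, and the event-only median is −ln(1 − c/2)/λ. For c = 0.25 and F = 5: λ = 0.0575 and the median is 0.1335/0.0575 = 2.32 years. Across c = 0.25 to 0.50, the median is 1.25–1.39 years for F = 3, 2.08–2.32 for F = 5 and 4.15–4.64 for F = 10. In this model it follows the length of follow-up and hardly reflects the success rate.

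**The case against.** The strongest reply is that the sentence on means and medians is general and does not name the two times. Kaplan-Meier and cumulative incidence curves are descriptive too, and the article condenses a full protocol that is not shown. It is true that no analysis set is stated, so restriction to women with the event is an inference. But the times are listed under descriptive statistics directly before the sentence that gives the summary measures, and no alternative is offered. The natural reading is a plain mean or median, and neither way of computing one avoids the bias. This is a stated method that does not suit the data, so the point goes beyond detail left to another document.

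The reply is right on several stronger readings that a reader might infer:

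- *That 75% of women (54 of 72) are lost to censoring.* That is the expected share without a live birth. Most of them may never have one, whatever the method. In the illustration, the would-be successes cut off are 35 − 21 = 14% of women in the first scenario and 35 − 30 = 5% in the second.
- *That 72 women will be transplanted.* The article aims for 100 girls undergoing cryopreservation and makes transplantation conditional. The number transplanted is not given.
- *That follow-up will be short.* Staggering follows from the design, but shortness does not. A girl aged 10 in 2024 is 36 in 2050.
- *That women lost to follow-up will be counted as failures.* No denominator rule is stated.

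It is also fair that a median among women who succeeded is a legitimate summary if labelled as such. The proposed analysis does not estimate the 1.39-year comparator directly: with 25–35% succeeding, a Kaplan-Meier median is not reached. For that reason the remedy is cumulative incidence at fixed times.

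**Conclusion.** The point holds. Following the text as written gives times to pregnancy and to live birth that are biased short, because follow-up after autotransplantation is staggered by design. The direction does not depend on the assumed values; the size does. The figures of 0.75 and 1.15 years against 1.39, and 21% and 30% against 35%, rest on 35% eventual success, exponential times with a mean of 2 years and uniform follow-up, none of which the documents state.

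The weight is moderate. Neither time appears among the primary, secondary or tertiary outcomes. A reader might infer that the primary outcome or the sample size is undermined, but the documents do not support that: the primary outcome is counts, and the 72 comes from the precision of a proportion. The crude counts remain valid as counts. They need a companion estimate that allows for follow-up before they are read as a chance of success.

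**What to change.** Analyse time to pregnancy and time to live birth as time-to-event from first autotransplantation, in all transplanted women. Censor at last contact or study end. Report cumulative incidence with 95% confidence intervals at fixed times (for example 1, 2 and 5 years), by Kaplan-Meier, or by Aalen-Johansen where a competing event such as death applies, beside the crude counts. If a mean or median among women with the event is also given, label it as conditional on the event.

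The cost is a change of wording and slightly more analysis work. The dates of transplantation, event and last contact must be recorded; the article does not say whether they already are. The sample size does not change.

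### Time to pregnancy and time to live birth are summarised by plain means or medians, which use only women with an observed event and run short when follow-up after grafting is truncated

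*Protocol article*

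**What the plan says.** Under Statistical analysis, the article applies descriptive statistics to the counts of pregnancies, miscarriages and live births after autotransplantation, to primordial follicle number, and to "time to pregnancy, and time to live birth". The next sentence fixes the form: "Continuous variables will be summarized as means with standard deviations (SD) or medians with interquartile ranges (IQR), depending on data distribution". Categorical variables are given as percentages. The only other method named for clinical data is correlation: "Associations will be assessed using Spearman’s correlation coefficient". No method for censored times is mentioned.

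Under Sample size calculation, the planning figures come from cancer survivors, in whom "pregnancy rates following transplantation of thawed ovarian cortical tissue are approximately 50% and live birth rates around 35" per cent. The calculation itself uses an "expected LBR of 0.25". The same section intends to use data from women lost to follow-up when it can.

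Study period gives a start in January 2024 and an expected end in 2050. The inclusion criteria admit girls aged 2–17 years. Autotransplantation takes place in adulthood, when pregnancy is being planned.

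**The concern.** A woman who has not conceived has no time to pregnancy, and a woman who has not delivered has no time to live birth. A plain mean or median therefore describes successes only. Two consequences follow.

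- **Who is described.** The figure says how long conception took in those who conceived. It does not say how long a grafted woman should expect to wait, because many may never have the event.
- **Bias from truncation.** If some women are observed for only a short time after grafting, late conceptions are missed more often than early ones. The observed times are then too short even for women who can conceive.

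The study as a whole is meant to support counselling, and the Discussion itself warns of false hope. A waiting time based on successes alone, without a label saying so, is easy to misread in that setting. It also sits badly with the wish to use data from women lost to follow-up: a plain mean or median cannot use a lost woman who had not conceived, whereas a censored analysis can, up to her last contact.

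**Working it through.** **1. The plan's own figure.** Inputs from Sample size calculation: p = 0.25, "a confidence interval width of 0.2" (W = 0.2) and α "of 0.025) the required sample size is 72, corresponding to 18 expected live births". With z = 1.960 (0.025 in each tail):

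n = 4z²p(1 − p)/W² = 4 × 3.8415 × 0.1875 / 0.04 = 72.03, so 72; and 72 × 0.25 = 18 live births.

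The stated figures are reproduced, and nothing below changes them.

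**2. Women left out at the planning rates.**
- Time to pregnancy: 1 − 0.50 = about 50%.
- Time to live birth: 1 − 0.25 = 75%, that is 72 − 18 = 54 of 72 if all 72 are grafted. At the 35% seen in cancer survivors it would be 65%.

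**3. Follow-up is unequal by design.** Girls entering in 2024 will be between 2 + 26 = 28 and 17 + 26 = 43 years old in 2050. Later entrants of the same age will be younger. Time between grafting and the end of the study will therefore differ widely and will often be short.

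**4. Size when some women can never conceive.** Assumptions, not in the article: half can ever conceive; among them times are exponential with median 2.0 years (λ = ln 2 / 2 = 0.3466 per year); follow-up is uniform over 0–10 years. Among women able to conceive, the probability of a pregnancy observed by time m is

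G(m) = 1 − e^(−λm) − [1 − e^(−λm)(1 + λm)]/(10λ).

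- G(10) = 0.9688 − 0.2483 = 0.7205, and half of that is 0.3602.
- G(1.40) = 0.3844 − 0.0247 = 0.3597, so the observed median is about 1.40 years against a true 2.0, which is 30% too short.
- Only 0.5 × 0.72 = 36% of grafted women contribute a time.

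A simulation (400,000 women per scenario) with a mean of 2 years in those able to conceive (true median 1.39) shows the range:

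| Follow-up | Median among observed conceptions | Shortfall |
|---|---|---|
| Complete | 1.39 years | none |
| Uniform 0–10 years | 1.10 years | 21% |
| Uniform 0–5 years | 0.84 years | 39% |

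The median in all grafted women is not reached in any of these.

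**5. Upper illustration: every woman would eventually have the event.** Assume a constant hazard and 5 years of follow-up for all, with a share p having the event by then: λ = −ln(1 − p)/5; true median = ln 2/λ; median among observed events = −ln(1 − p/2)/λ.
- p = 0.50: λ = 0.1386; true 5.0 years; observed 0.2877/0.1386 = 2.1 years.
- p = 0.25: λ = 0.0575; true about 12 years (extrapolated); observed 0.1335/0.0575 = 2.3 years.

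**6. Does a censored method recover the truth?** With a constant hazard, follow-up uniform over 0–10 years and 50% observed to conceive, the simulated median among conceivers is 2.0 years, the true median 4.3 years and the Kaplan–Meier median 4.3 years.

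**The case against.** The strongest reply is that the restriction to women who conceive is inferred. The article does not state it, gives no denominator or censoring rule, and a median with quartiles can be read from a Kaplan–Meier curve. Such details often belong to an analysis plan, which is not shown. This stands in part: the text does not literally exclude a censored analysis. But the article goes beyond silence. It names these times and then gives a summary rule for continuous variables, with the choice between mean and median left to the data distribution. The plain reading is a mean or median of observed times.

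Several limits stand in full:

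- With complete follow-up, the time among women who conceive is a valid conditional figure. What remains then is labelling, not bias.
- Women without a pregnancy are not hidden, because counts and percentages are reported alongside. Those percentages do not correct the times, however.
- The times are not among the primary, secondary or tertiary outcomes.
- No section says that these times will be presented as the expected wait after grafting.

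Two stronger readings are tempting. A reader might infer that the flaw undermines a planned relation of these times to karyotype, age or hormones. The article plans no such relation: the Primary outcome section relates the counts to those factors, Secondary outcomes does so for follicle density, and the correlation example concerns age, hormones and follicle number. A reader might also take 5.0 against 2.1 years, or 12 against 2.3, as the expected error. Those contrasts need every grafted woman to have the event eventually, and nothing in the article supports that.

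**Conclusion.** The point holds as a correction to a descriptive analysis. As written, the two summaries leave out about half of grafted women for pregnancy and about three quarters for live birth, at planning rates that are not observed Turner syndrome rates after grafting. With truncated follow-up, the times are also too short for women able to conceive: by 21% to 39% in the scenarios with a fraction who never conceive (1.4 against 2.0 years in the main example). The size rests on assumed time scales and follow-up patterns; the direction rests on the staggered ages and the fixed end of study. The constant-hazard contrasts mark only an upper illustration. The primary counts and the sample size of 72 are unaffected.

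**What to change.** Replace the plain mean or median for these two variables as follows:

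- Measure time from autotransplantation to first pregnancy and to first live birth in all grafted women.
- Censor at last contact or end of study.
- Report Kaplan–Meier or cumulative incidence estimates with 95% confidence intervals at prespecified times (for example 12, 24 and 60 months; the choice is the sponsor's). Give a median only if it is reached.
- Label any time shown among women who conceived as conditional on conception.

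The cost is a change of wording and slightly more analysis work. The dates of grafting and event are needed for the planned summaries anyway; the date of last contact must also be kept for women without an event. The reported times will look less favourable.

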## Discussion

Assessing ovarian activity and predicting future ovarian function in girls with TS remains challenging. In the context of OTC, a key difficulty is identifying which girls are most likely to benefit from the procedure. Although AMH levels are associated with karyotype, FSH/LH levels, and the presence of follicles [12, 14, 22, 36], and low AMH levels are associated with absent puberty and imminent POI in TS [13, 36], the overall predictive value of AMH remains uncertain. In one study of seven girls with TS undergoing ovarian stimulation and oocyte cryopreservation [37], no association was found between AMH levels, antral follicle count, and the number of oocytes retrieved. Remarkably, all participants had available oocytes for cryopreservation despite AMH levels as low as 3.05 pmol/L. In a Dutch cohort of girls with TS who underwent OTC [38], AMH was the best predictor of follicles present in the ovary removed for cryopreservation. Only 6% (4/67) of girls with undetectable circulating levels of AMH had ovarian follicles, and the density of follicles was very low [38]. Importantly, the chromosomal constitution of ovarian cells does not necessarily match that of peripheral lymphocytes or other tissues (e.g. buccal cells). Thus, the proportion of affected cells in peripheral blood is not always predictive of the remaining pool of primordial follicles. This may explain the occasional spontaneous pregnancies in women with complete 45,X monosomy [39]. Peek et al. [40] analyzed 46 oocytes from 10 women with TS and found that while 90% of the oocytes were correctly tetraploid (arrested in prophase of meiosis I), the surrounding granulosa cells were predominantly 45,X. These findings imply that although AMH levels and karyotype are useful indicators of ovarian function and the presence of follicles, they are not sufficient as stand-alone predictors. Follicles may still be present, and potentially usable for OTC, even in individuals with low AMH levels or complete 45,X monosomy in peripheral lymphocytes. This underscores the need for further research into ovarian mosaicism and the identification of more reliable biomarkers for assessing ovarian function and determining eligibility for OTC in girls with TS.

The timing and mechanisms underlying the loss of ovarian function in TS are not fully understood. Of particular interest are X-linked genes such as *KDM6A*, *USP9X*, and *ZFX*, which play critical roles in germ cell development and escape X inactivation. These genes have been found to be either differentially methylated [41] or differentially expressed [42] in adult women with TS compared to 46,XX controls, based on analyses of DNA from leukocytes or fibroblasts. However, as gene expression and methylation patterns are highly tissue-specific, it is essential to replicate these analyses in ovarian tissue. We plan to perform genomic analyses on a portion of the excised ovarian tissue to gain further insight into the molecular mechanisms underlying ovarian dysgenesis in TS.

Since most individuals with TS who have undergone OTC have not yet reached an age at which pregnancy is typically pursued, long-term reproductive outcomes remain unknown. To date, no live births have been reported in women with TS following autotransplantation of cryopreserved and thawed ovarian cortical tissue. One case report has described a clinical pregnancy in a woman with TS following re-implantation of autologous ovarian cortex cryopreserved shortly after spontaneous puberty; unfortunately, it resulted in an early miscarriage at approximately seven weeks of gestation [20]. As such, the procedure remains experimental in this population, and the absence of clinical evidence poses important ethical challenges and complicates the counselling of eligible girls and their families. In prepubertal girls, OTC requires laparoscopic unilateral oophorectomy, which carries a small risk of surgical complications, including bleeding and infection. Moreover, if autotransplantation does not lead to pregnancy, the procedure may generate false hope and increase the risk of future distress [43, 44]. A further concern is that removal of one ovary at a young age may accelerate the depletion of an already severely compromised ovarian reserve. Although studies in the general population suggest that unilateral oophorectomy only advances the age of menopause by approximately 1–2 years [45, 46], these findings may not be generalizable to girls with TS, who typically undergo oophorectomy at a much earlier age and are inherently at risk of POI. In a recent prospective follow-up study of 28 girls with TS who underwent OTC, van der Coelen et al. [47] investigated whether the natural progression of puberty was affected. The authors argued that pubertal development proceeded largely as expected based on age, karyotype, and pre-OTC hormonal status. However, the longest follow-up was only 6.6 years, and several participants had not yet reached the age at which the onset – or absence – of puberty could be evaluated. Interestingly, in most girls, AMH levels declined during the first year following OTC, before stabilizing or increasing – in some cases exceeding pre-OTC levels. The pattern was most pronounced in prepubertal girls. Further research is needed to elucidate the longitudinal trends of AMH following OTC and the clinical implications. Taken together, these factors underscore the need for caution and comprehensive counselling when offering experimental fertility preservation in TS, particularly considering the current lack of evidence on long-term outcomes following OTC.

The Danish Turner Syndrome Cryopreservation Study represents an important step toward understanding the potential and limitations of OTC in TS. By prospectively following girls with TS across the full spectrum of ovarian function – including those not deemed eligible for OTC – the study will provide valuable insights into the progression of ovarian insufficiency, as well as long-term reproductive outcomes following OTC and subsequent autotransplantation. These findings will help refine patient selection, enhance clinical counselling, and support evidence-based decision-making regarding fertility preservation in this population.

